## 9.3 Analysis for the secondary endpoints

Analysis of the secondary endpoints will be based on the intention-to-treat principle by treatment group.

### 9.3.1 Analysis for categorical and ordinal endpoints

#### **Binary variables include:**

- The incidence and severity of gastric and intestinal mucosal lesions during the first 6 months after study enrollment (prior to randomization);
- The incidence and severity of gastric and intestinal mucosal lesions after randomization (ie, between 6 months and 12 months after study enrollment);
- The incidence of clinically evident gastrointestinal hemorrhage attributed to the upper GI tract (or of unknown origin) during 6 months after study enrollment (prior to randomization);
- The incidence of clinically evident gastrointestinal hemorrhage attributed to the upper GI tract (or of unknown origin) after randomization (ie, between 6 months and 12 months after study enrollment);
- The incidence of clinically evident gastrointestinal hemorrhage attributed to the upper GI tract (or of unknown origin) during 12 months after study enrolment.

Binary variables will be analyzed using logistic regression with treatment as fixed effect factors. Logistic regression model results will be reported as odds ratios for monotherapy group vs. DAPT group, with 95% CIs and p-values.

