## **15. APPENDIX 1- DEFINITION FOR STUDY**

### **ENDPOINTS**

#### **15.1 Definition of erosion and ulcer**

Gastrointestinal erosion is defined as superficial mucosal breaks with a diameter of  $\leq 5$  mm. Gastrointestinal ulcer is defined as a mucosal break with a diameter  $\geq 5$  mm, typically covered with fibrin.

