## 16. APPENDIX 2 - MAGNETICALLY CONTROLLED CAPSULE ENDOSCOPY SCORING SYSTEM

### 16.1 The gastric mucosal injury is evaluated through the Lanza score

**Table 6 Lanza score**

| Endoscopic manifestation                                                   | score |
|----------------------------------------------------------------------------|-------|
| No erosion                                                                 | 0     |
| 1–2 erosions localized in the gastric antrum, body or bottom               | 1     |
| 3–5 erosions localized in one area of the stomach                          | 2     |
| Erosions localized in 2 different areas of the stomach (total 6–9 lesions) | 3     |
| Gastric ulcer or ≥ 10 erosions                                             | 4     |

Efficacy evaluation standard:

the proportion of mild gastric mucosal injury = cases with 1 point and 2 points / total cases × 100%

The proportion of severe gastric mucosal injury = cases with 3 points + 4 points / total cases × 100%

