### **2.3 Exploratory Objectives**

The exploratory objective is to establish a gastrointestinal mucosal injury scoring system that may identify patients at future risk for clinical gastrointestinal bleeding during long-term APT.

For this purpose, 2 previously developed scoring systems will be used to assess the degree of mucosal injury observed by AMCE: (1) The modified Lanza score (MLS), and (2) a separate 5-point scoring system (See in protocol Appendix 2).

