#### **Ordinal variables include:**

- Gastrointestinal symptoms (pain, nausea/vomiting, dysphagia, other) during the 12 months after enrolment (Protocol Appendix 3).

Ordinal outcomes will be compared between groups using proportional odds logistic regression models. Logistic regression model results will be reported as odds ratios for monotherapy group vs. DAPT group, with 95% CIs and p-values.

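### SAP 9.3.1 analyses lesion severity, graded on two ordered 0–4 scales, as a binary variable without naming a cut; the gastric score and the 5 mm boundary also need completing

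*Supplement*

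**What the plan says.** SAP 9.3.1 joins incidence and severity in one endpoint, for the periods before and after randomisation, and lists it as binary. The post-randomisation entry begins "The incidence and severity of gastric and intestinal mucosal lesions after randomization". The method for the whole list is: "Binary variables will be analyzed using logistic regression with treatment as fixed effect factors".

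The next list in the same section is for ordinal variables, and gastrointestinal symptoms are its only entry. There the SAP states: "Ordinal outcomes will be compared between groups using proportional odds logistic regression models".

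SAP 2.3 says that "2 previously developed scoring systems will be used to assess the degree of mucosal injury observed by AMCE" and refers to Protocol Appendix 2. In protocol V1.4 that appendix holds two scales, each from 0 to 4:

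- **Stomach (16.1, Table 6).** Score 2 is 3–5 "erosions localized in one area of the stomach". Score 3 is "Erosions localized in 2 different areas of the stomach", with 6–9 lesions in total. Score 4 is a gastric ulcer or at least 10 erosions. Scores 1–2 count as mild and 3–4 as severe.
- **Small intestine (16.2, Table 7).** Five ordered categories, from normal to large erosion or ulcer. No mild/severe split is given.

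Protocol 15.1 reads "Gastrointestinal erosion is defined as superficial mucosal breaks with a diameter of" 5 mm or less, and sets ulcer at 5 mm or more. SAP 4.1 sets erosion below 5 mm and ulcer at 5 mm or more.

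**The concern.** The primary endpoint counts a single erosion the same as an ulcer or a bleed. Severity after randomisation is the lesion endpoint that can show whether monotherapy reduces the extent of injury as well as its presence. As written, three things are left to the analyst or the reader of the images:

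1. What the binary severity variable is. For the stomach one can guess the Appendix 2 split; for the small intestine there is nothing to guess from.
2. Which score to give gastric patterns that Table 6 does not cover, at the very point where mild becomes severe.
3. Whether a 5 mm lesion is an erosion or an ulcer. That label decides gastric score 4. It also decides entry, because ulceration bars enrolment (protocol 5.2) and randomisation (protocol 5.3, SAP 3.3), while the AMCE condition in those sections names only ulceration and bleeding, not erosion.

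**Working it through.** **Step 1. The plan's own figure.** Inputs from SAP section 5: 47% v 30%, 1:2 allocation, two-sided 0.05, 90% power, 20% loss. The pooled rate is (0.47 + 2 × 0.30)/3 = 0.357.

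n(DAPT) = [1.96 √(0.357 × 0.643 × 1.5) + 1.282 √(0.47 × 0.53 + 0.30 × 0.70/2)]² / 0.17² = 126.6, so 127 + 254 = 381, against 384 stated. With 128 + 256, power is 0.903. 384/0.80 = 480. The stated sample size reproduces. The documents state no power for severity.

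**Step 2. Is Table 6 complete?** I crossed 1–9 erosions (no ulcer) with 1, 2 or 3 gastric areas, the three areas being those named in the score 1 row.

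| Erosions | 1 area | 2 areas | 3 areas |
|---|---|---|---|
| 1–2 | 1 | none for 2 erosions, on a strict reading | – |
| 3–5 | 2 | none | none |
| 6–9 | none | 3 | none |

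Of 24 possible patterns, 15 have no score. Within 3–9 erosions it is 14 of 21. The two groups that matter most are 3–5 erosions in two areas and 6–9 in one area. Both lie between score 2 (mild) and score 3 (severe), so their class is undefined. The documents do not say how often they occur.

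**Step 3. What does a severe/not split cost?** The documents give no score distribution, so this is illustration only. Assumptions: 128 v 256 evaluable patients; 53% of DAPT patients at score 0 (1 − 0.47); one common odds ratio at every cut, equal to the planned one, (0.30/0.70)/(0.47/0.53) = 0.483, with |ln OR| = 0.727; and three spreads of the other 47% over scores 1–4.

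Ordinal model (Whitehead): V = n₁n₂N / [3(N+1)²] × (1 − Σp̄³), and power = Φ(|ln OR| √V − 1.96). For the middle spread Σp̄³ = 0.272, so V = 28.30 × 0.728 = 20.6 and power = Φ(0.727 × 4.54 − 1.96) = Φ(1.34) = 0.91.

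Severe v not (two proportions, same spread): 15.0% v 7.9%, standard errors 0.0328 (null) and 0.0358 (alternative), power = Φ[(0.0714 − 1.96 × 0.0328)/0.0358] = 0.58.

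| DAPT scores 1/2/3/4 (%) | Severe, DAPT v mono | Ordinal | Any v none | Severe v not |
|---|---|---|---|---|
| 30/10/4/3 | 7.0% v 3.5% | 0.91 | 0.90 | 0.35 |
| 20/12/8/7 | 15.0% v 7.9% | 0.91 | 0.90 | 0.58 |
| 10/10/12/15 | 27.0% v 15.2% | 0.91 | 0.90 | 0.78 |

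**Step 4. The 5 mm boundary.** Under protocol 15.1 a lesion of exactly 5 mm meets both definitions; under SAP 4.1 it is an ulcer only. The two current documents disagree.

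**The case against.** **Appendix 2 already defines a binary severity variable.** For the stomach it does, and a prespecified proportion severe is a coherent choice. But the SAP does not say that it uses it, and the small intestine has no counterpart. A reader might infer that the SAP cuts both scores between 2 and 3; no text says so.

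**The ordinal model mostly re-tests incidence.** This stands. In step 3 its power is 0.91 against 0.90 for any lesion: the any-lesion split carries (128 × 256/384) × 0.357 × 0.643 = 19.6 of the 20.6 units of information in the middle spread. If treatment changed severity only among patients who have lesions (an assumed 40% in each arm, odds ratio 2), a rank test over all patients has power of just 0.07–0.11, and severe v not 0.27–0.38. The split should therefore be kept as a supporting analysis.

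**A larger loss can be made to appear.** With an assumed DAPT distribution of 30/25/20/15/10% over scores 0–4 and an odds ratio of 0.6, power is 74% ordinal, 49% severe v not and 61% any v none. That puts 70% of DAPT patients above score 0, while the plan expects 47% with any lesion in either organ. It should not be used for the gastric score.

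**Reading is blinded and the scores are reported.** A blinded core laboratory reads all images (SAP 3.4.1), a blinded committee adjudicates lesions (protocol 12.4), and the table listings show both scores at all three examinations. Blinding makes an ad hoc rule unlikely to favour an arm. It does not supply the missing rule, and listing the scores is not an analysis of them.

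**The 5 mm point is settled for analysis.** SAP 4.1 does settle it there, and the primary composite counts either lesion. What remains is the conflict with the protocol.

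**Conclusion.** The point holds for a secondary endpoint. Severity has no defined binary form for the small intestine and none named in the SAP for the stomach, although a suitable ordinal model is already specified in the same section. Table 6 is incomplete at its mild/severe boundary, and the two documents disagree at 5 mm.

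Under the step 3 assumptions, severe v not has power of 0.35–0.78 where the ordinal model has 0.91. This rests on assumed spreads and on proportional odds, and shows direction only. Three stronger readings are not supported: that the unscored patterns are common, since no frequency is given; that the ordinal model gains materially over incidence; and that the primary result or its sample size is at risk.

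**What to change.** 1. In SAP 9.3.1, separate incidence from severity. Keep incidence binary. List post-randomisation severity as ordinal, with one proportional odds analysis for the gastric score and one for the small-intestinal score.
2. Keep the Appendix 2 gastric proportion severe (3–4) as a named supporting analysis.
3. Before unblinding, add a rule that gives every erosion count-by-area pattern exactly one Table 6 score. The documents do not show which completion is right, for example scoring on count alone, so the core laboratory should settle it.
4. Reconcile protocol 15.1 with SAP 4.1 on lesions of exactly 5 mm.

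The cost is wording in the SAP and the protocol appendices. The model is already planned for symptoms and needs no new method. The downside is a proportional odds assumption that has to be checked for each score.

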### 16.2 Five-point scoring system for small intestinal mucosal injury

**Table 7 Five-point scoring system to assess intestinal mucosal injury**

| Category                                                                                             | Score |
|------------------------------------------------------------------------------------------------------|-------|
| Normal                                                                                               | 0     |
| Petechiae/red spot (demarcated, usually circular, area of crimson mucosa with preservation of villi) | 1     |
| Small number of erosions (1–4 erosions)                                                              | 2     |
| High number of erosion (>4 erosions)                                                                 | 3     |
| Mucosal breaks (large erosion and/or ulcer)                                                          | 4     |

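### SAP 9.3.1 analyses lesion severity as a binary variable although it is graded on two 0–4 ordinal scores; no cut is prespecified for the small intestine, and a gastric split loses grade information

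*Supplement*

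**What the plan says.** Secondary endpoints 1 and 2 (SAP 4.2) each cover both how often lesions occur and how severe they are, before and after randomisation respectively. SAP 9.3.1 places both among the binary variables. The post-randomisation entry reads "The incidence and severity of gastric and intestinal mucosal lesions after randomization (ie, between 6 months and 12 months after study enrollment", and the model for the whole list is: "Binary variables will be analyzed using logistic regression with treatment as fixed effect factors".

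The same section has a second model: "Ordinal outcomes will be compared between groups using proportional odds logistic regression models". Its list holds one item, gastrointestinal symptoms.

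Severity grading appears elsewhere. SAP 2.3, under the exploratory objective, says that "2 previously developed scoring systems will be used to assess the degree of mucosal injury observed by AMCE" and points to Protocol Appendix 2:

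- **Stomach (Protocol 16.1).** The Lanza score runs from 0 to 4, with top grade "Gastric ulcer or ≥ 10 erosions". Two summary classes follow: "the proportion of mild gastric mucosal injury = cases with 1 point and 2 points" and "The proportion of severe gastric mucosal injury = cases with 3 points + 4 points".
- **Small intestine (Protocol 16.2).** The "Five-point scoring system to assess intestinal mucosal injury" also runs from 0 to 4. It has no mild or severe class and no cut-point.

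SAP section 11 (item 2.1.9) tabulates both scores at baseline, 6 and 12 months for the randomised cohort. It names no test.

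**The concern.** The stated model does not fit the outcome. Binary logistic regression needs a yes/no variable, and SAP 9.3.1 names neither a score nor a cut. It also does not say whether stomach and intestine are analysed separately or combined.

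For the intestine, the analyst would have to choose among four possible cuts. The lowest is not a neutral default: intestinal score 1 is petechiae or a red spot, whereas the endpoint in SAP 4.2 is built from erosion, ulceration and bleeding. Protocol 5.5.3 has a first unblinding step that sorts patients into groups A, B and C for the analysis. A cut still open at that point could be chosen with the arms already separated.

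The primary endpoint counts one small erosion the same as an ulcer, and patients with erosions at 6 months may be randomised (SAP 3.3 bars only ulceration or bleeding). Post-randomisation severity is therefore the endpoint that should show whether monotherapy shifts the grade of injury. A single split uses only part of that information.

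**Working it through.** **1. Inputs.** From SAP 5: 47% versus 30% with the primary endpoint; 128 DAPT and 256 monotherapy patients evaluable; two-sided alpha 0.05; stated power 90%. From Protocol 16.1 and 16.2: five grades per score. Neither document gives a score distribution or a severity effect, so both are assumed below.

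**2. The plan's own figure.** Two-proportion test with pooled variance under the null:

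- Pooled p = (0.47×128 + 0.30×256)/384 = 0.3567
- SE under H0 = √[0.3567×0.6433×(1/128 + 1/256)] = 0.0519
- SE under H1 = √[0.47×0.53/128 + 0.30×0.70/256] = 0.0526
- z = (0.17 − 1.96×0.0519)/0.0526 = 1.30, so power = 90.3%

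This agrees with the stated 90%. No power is stated for severity.

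**3. What can be run as written.**

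| Component | Yes/no variable defined? |
|---|---|
| Incidence, either organ | Yes: any lesion or none |
| Gastric severity | Classes in Protocol 16.1, not adopted in SAP 9.3.1 |
| Intestinal severity | No cut in either document |

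**4. Power under proportional odds (assumed).** Common odds ratio = (0.30/0.70)/(0.47/0.53) = 0.483, applied at every grade boundary. The DAPT arm has 53% at score 0. Ordinal power by the Whitehead approximation is Φ(|ln OR|×√V − 1.96), with V = [n1·n2/(3N)]×(1 − Σ p̄³), where p̄ is the pooled share in each grade.

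Example, DAPT split 53/25/12/6/4:

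- n1·n2/(3N) = 128×256/1152 = 28.44
- Σ p̄³ = 0.275, so V = 20.6
- 0.727×4.54 − 1.96 = 1.34, so power = 91%

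Severe cut (≥3) in the same case: 10% becomes 5.1%. Then z = (0.0490 − 1.96×0.0271)/0.0299 = −0.14, so power = 45%.

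| DAPT % at scores 0/1/2/3/4 | Severe, DAPT vs mono | Ordinal | Severe cut | Any lesion |
|---|---|---|---|---|
| 53/30/12/3/2 | 5% vs 2.5% | 91% | 28% | 90% |
| 53/25/12/6/4 | 10% vs 5.1% | 91% | 45% | 90% |
| 53/15/12/10/10 | 20% vs 10.8% | 91% | 68% | 90% |
| 53/8/8/12/19 | 31% vs 17.8% | 91% | 82% | 90% |

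Simulation (2,000 trials per row, rank test against chi-square) gave 91–93% ordinal; 28%, 46%, 71% and 83% for the severe cut; and 90–91% for any lesion.

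**5. Power when proportional odds fails.** Severe injury falls from 20% to 10% in each case, with a weaker or no effect on having any lesion:

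| DAPT | Monotherapy | Ordinal | Severe cut | Any lesion |
|---|---|---|---|---|
| 53/25/2/10/10 | 63/25/2/5/5 | 65% | 77% | 49% |
| 50/20/10/10/10 | 50/25/15/5/5 | 13% | 76% | 5% |
| 53/15/12/10/10 | 60/16/14/5/5 | 44% | 77% | 26% |

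The ranking of ordinal test and severe cut reverses in all three.

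**The case against.** A reader might go further and infer that the severity endpoint cannot be run at all, that gastric severity is underpowered, that three of the four gastric boundaries are thrown away, or that the 6-month score is never used. The documents support none of these.

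- Incidence runs as written, and intestinal severity would run once a cut was fixed. Only a prespecified intestinal severity test is absent.
- Incidence (roughly ≥1) together with the severe class (≥3) retains two of the four gastric boundaries.
- The 6-month scores are tabulated, and SAP 9.5 explores predictors of injury at 6 months. What is missing is the score as a covariate, and treatment-only models are the SAP's consistent choice.
- The power loss is not a document figure. The odds ratio comes from a 12-month composite across both organs that includes lesions before randomisation. The ordinal advantage is built into the common shift, and any lesion alone already reaches about 90% on those assumptions.
- The two scores are introduced under the exploratory objective. Linking them to secondary endpoints 1 and 2 is an inference.

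All of this stands as a limit on the claim. The mismatch remains: no other severity measure exists, the intestinal variable is undefined, and the suitable model sits in the same section but is assigned to symptoms alone.

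**Conclusion.** The point holds as a mismatch between outcome and model in part of two secondary endpoints. It is firm for the small intestine, where no binary severity variable is defined. For the stomach, usable classes exist but SAP 9.3.1 does not adopt them, and any single split loses grade information.

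The efficiency gain is conditional. Under proportional odds with the assumed odds ratio and 47% injured on DAPT, the ordinal model gains about 9 to 63 percentage points over the severe cut (91 − 82 and 91 − 28), but only about one point over any lesion. If the effect is concentrated in severe grades, the severe cut is the stronger test. The better-supported reasons for change are therefore prespecification and use of the full grade. The change is worth making before unblinding; it does not touch the primary endpoint, its test or the sample size.

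**What to change.** Before unblinding, amend SAP 9.3.1 as follows:

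1. Keep lesion incidence in the binary list. Move post-randomisation severity to the ordinal list and state that it is measured by the Protocol Appendix 2 scores.
2. Analyse the 12-month Lanza score and the 12-month intestinal score separately, each by proportional-odds regression with arm and the patient's own 6-month score as covariates.
3. Prespecify a check of the proportional-odds assumption, and report the full grade distribution by arm.
4. Keep severe gastric injury (score 3–4) as a supportive binary result. This also guards against an effect confined to the severe grades.

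If the sponsor prefers a binary analysis, the minimum is one stated cut per organ, fixed before any group codes are released.

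The cost is a few lines of SAP text and one model per score, using data already collected. The price is reliance on proportional odds, which the SAP already accepts for symptoms.

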#### **Ordinal variables include:**

- Gastrointestinal symptoms (pain, nausea/vomiting, dysphagia, other) during the 12 months after enrolment (Protocol Appendix 3).

Ordinal outcomes will be compared between groups using proportional odds logistic regression models. Logistic regression model results will be reported as odds ratios for monotherapy group vs. DAPT group, with 95% CIs and p-values.

### 9.3.2 Analysis for time-to-event endpoints

Kaplan-Meier curves will be plotted by treatment group. Patients not experiencing a endpoint event during corresponding time interval will be censored at the time of death, last contact date (for subjects withdrawing consent or lost to follow-up) or 365 days, whichever comes first.

A hazard ratio (HR) and two-sided 95% CI for the primary endpoint will be generated using the Cox proportional hazards model. The null hypothesis ( $H_0$ ) for this analysis is that the  $HR = 1$ . The two-sided alternative hypothesis ( $H_A$ ) is that the  $HR \neq 1$ . A test of superiority at the two-sided 0.05 level will be performed using a p-value from a log-rank test.

- All bleeding (BARC types 1–5) during the 12 months after enrollment;
- The incidence of target lesion failure (TLF); cardiac death, target-vessel MI, or clinically-driven target lesion revascularization), during the 12 months after enrollment;
- The incidence of net adverse clinical events (NACE, defined as TLF or BARC type 2–5 bleeding) during the 12 months after enrollment;
- The incidence of stent thrombosis (ARC definite, probable, or definite/probable) during the 12 months after enrollment.

In addition, all secondary endpoints will also be compared across the 3 groups, and for all single group versus group comparisons (12-month DAPT vs 6-month DAPT plus 6-month aspirin monotherapy; 12-month DAPT vs 6-month DAPT plus 6-month clopidogrel monotherapy; and 6-month DAPT plus 6-month aspirin monotherapy versus 6-month DAPT plus 6-month clopidogrel monotherapy).

All analysis will be repeated in the PPS to support the primary results.

